#### Exclusion Criteria

Participants meeting any of the following aspects will be excluded:

A history of abdominal or anorectal surgery;Irritable bowel syndrome and organic or drug-induced constipation; secondary to endocrine, metabolic or neurotic constipation;Patients with severe cardiovascular, hepatic, or renal diseases or cognitive impairment, aphasia, or unable to cooperate with sample collection and treatment;Patients with other primary diseases caused by intestinal microbial disorder (diabetes, obesity, migraine, polycystic ovary syndrome, etc.);Patients during pregnancy, lactation, or with a pregnancy plan in 3 months;Patients with blood coagulation dysfunction or using anticoagulants, such as Warfarin and Heparin.

### Informed Consent

When signing the informed consent, all subjects will be informed that they would be randomly assigned to VA or SA acupuncture group, with possible benefits and risks. All subjects will voluntarily sign the informed consent before participating in this study and can withdraw from the study at their discretion.

### Sample Size, Randomization and Blinding

#### Calculation of Sample Size

The formula for calculating the sample size in clinical trials is not available in the presented study. In most similar studies devoted to microRNAs and gut microbiota, the sample size is mainly 30 cases to obtain outcomes with statistical significance (24). Considering the need for further miRNA validation in an expanded cohort plus a drop-out rate of 20%, the sample size in this setting is determined to be 80 cases (40 per). Accordingly, the number of healthy volunteers will be 40 cases, with matched demographic characteristics such as age and sex.

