### Trial Design

This trial is designed as a randomized, sham-controlled trial with blinded participants, outcome assessor, and statistician. In this study, 80 eligible participants will be randomized to the verum acupuncture (VA) or sham acupuncture (SA) group with a ratio of 1:1. The total research period will be preceded by a 1-week run-in phase after the screening visit, then following the 4-week treatment phase, and 4-week follow-up phase. Forty healthy volunteers will also be enrolled to serve as a healthy control group. Healthy volunteers will not receive any treatment, and the correlation between gut microbiota and fecal miRNAs will be determined by comparing the constipated patients before treatment with them. The time frame of this trial is presented in Table 1.

**Table 1 T1:** Time points of treatment assessment.

	**Enrollment**	**Baseline**	**Treatment phase**		**Follow-up phase**			
**Time point**	**Week −1**	**Week 0**	**Week 2**	**Week 4**	**Week 5**	**Week 6**	**Week7**	**Week 8**

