#### Randomization

SCC participants will be divided into verum and sham acupuncture groups based on a randomization allocation card, which will be filled according to the random sequences generated by SPSS 25.0 software, including terms of random numbers, serial numbers, and allocation information, and enveloped and provided by visit order. The healthy subjects will be directly recruited as the healthy control without randomization.

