#### Gut Microbiota Analysis

The 16S rRNA third-generation full-length sequencing technology will be used to analyze the variations in intestinal microbiota (20–22). Sequencing will be performed on the V4 region and the V3 to V4 amplification region of the 16S rRNA gene. Purified amplicons will be pooled in equimolar amounts and paired-end sequenced (2 × 250) on an Illumina MiSeq 2500 platform (Illumina, San Diego, USA) according to standard protocols. After screening, the clean sequences will be clustered into operational taxonomic units (OTUs) based on 97% identity using Uparse (version 7.0.1001). Rarefaction curves for alpha diversity will be generated to assess the efficiency of sequencing depth. Species richness and diversity will be estimated using the observed species, Chao1, Shannon index, and Simpson index. Principle coordinate analysis and partial least-squares discriminant analysis will be used to reveal differences in OTU levels between samples. The linear discriminant analysis effect size will be performed using the non-parametric factorial Kruskal–Wallis sum-rank test to assess the effect size of each differential OUT.

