#### MicroRNAs High-Throughput Sequencing Analysis

High-throughput sequencing using stool samples will be performed for miRNA expression profiling to determine candidate miRNA biomarkers for the efficacy of acupuncture (24–26). Fecal miRNA levels initially will be determined using a TaqMan low-density array in pooled samples. Markedly altered miRNAs in participants will subsequently be validated using quantitative real-time polymerase chain reaction on individual samples. Agilent 2100 will be used for detection, and after qualification, these fragments will be sequenced using the Illumina NOVA platform. Bowtie software will be employed to classify and annotate sRNA, and unannotated reads will be obtained by comparing clean reads with the database. The difference between SCC patients and healthy volunteers at baseline will be analyzed to explore potential biomarkers associated with the development of SCC. Within the pool of biomarker candidates related to SCC, the difference between VA and SA at week 4 will be compared, to determine biomarkers related to the clinical efficacy.

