#### Tripartite Network Analysis

The tripartite network analysis will be used to integrate information from the fecal microRNA characteristics, specific gut microbiota, and clinical data for constipated patients in the VA and SA groups. The interaction among the clinical efficacy (amelioration of SCC symptoms), microRNA characteristics (the differential expression of miRNAs in the stool), and fecal microbiome (stool microbial community) will be investigated by computing Spearman's correlations in Matlab (version R2015b). An effect size of *r* = 0.10 is considered less (1% variance explained), 0.30 moderate (9% variance explained), and 0.50 large (25% variance explained). Fisher's *r*-to-*z* transformation will be adopted to investigate the correlation coefficient difference between groups (acupuncture-sham acupuncture), using the *Z*-test. Significance will be considered at uncorrected *p* < 0.05. The Cytoscape (version 3.8.2) will be used to generate and visualize the phenome, fecal microbiome, and differentially expressed miRNAs interaction network. The networks will be presented based on selecting the gut microbiota counts and their first neighbors as nodes and all adjacent edges. The results will be shown in the line with direct (correlations with fecal microbiome) and indirect effects (clinical symptoms and differentially expressed miRNAs) with an emphasis on the association between microbiome and clinical efficacy. The comparisons between groups will be analyzed using one-way analysis of variance and independent sample *t-*test.

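### Healthy controls are matched on age and sex, but every group test the protocol names is unadjusted; the baseline patient-healthy contrast should carry the matching factors as terms

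*Protocol article*

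**What the plan says.** **Design.** Under Calculation of Sample Size, the healthy group is fixed as follows: "Accordingly, the number of healthy volunteers will be 40 cases, with matched demographic characteristics such as age and sex". Under Randomization: "The healthy subjects will be directly recruited as the healthy control without randomization". Neither place says whether matching is individual or by frequency.

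**Use of the controls.** Trial Design states that "the correlation between gut microbiota and fecal miRNAs will be determined by comparing the constipated patients before treatment with them". The miRNA section adds: "The difference between SCC patients and healthy volunteers at baseline will be analyzed to explore potential biomarkers". The verum-sham comparison at week 4 is then made only among the candidates found in that step.

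**Named tests.**
- Clinical Data Analysis: chi-square for qualitative data; ANOVA, or Mann-Whitney if data are not normal, for quantitative data.
- Gut Microbiota Analysis: the linear discriminant effect-size step "will be performed using the non-parametric factorial Kruskal–Wallis sum-rank test".
- Tripartite Network Analysis: "The comparisons between groups will be analyzed using one-way analysis of variance and independent sample" t-test.
- MicroRNAs High-Throughput Sequencing Analysis: no test is named for the patient-healthy contrast.

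No covariate-adjusted, stratified or paired analysis appears anywhere in the article.

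**The concern.** By matching on age and sex, the design treats them as factors that could distort the patient-healthy contrast. That contrast is observational, and matching is its only protection against those two factors. The named tests then ignore them, which can go wrong in two ways.

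- **Matching works and the factors predict the marker.** The design has removed age and sex from the contrast, but the test leaves their variance in the error term. The test is conservative and loses power.
- **Matching is imperfect.** The remaining age or sex difference is not corrected, and part of it is counted as a disease effect.

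The miRNA contrast acts as a gate. A marker missed there never reaches the week-4 acupuncture comparison, and one admitted because of age or sex is labelled as related to constipation.

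**Working it through.** **Inputs from the protocol.** 80 patients before treatment and 40 healthy volunteers. Significance level 0.05; the protocol states it, uncorrected, for the network correlations, and two-sided use here is an assumption.

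**Inputs assumed, because the protocol gives none.** R2, the share of a marker's variance explained by age and sex. The age or sex gap left after matching, in SD units. A true difference of 0.5 SD for power.

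**The plan's own figure.** The sample size starts from 30 cases ("the sample size is mainly 30 cases to obtain outcomes with statistical significance") and 20% drop-out ("plus a drop-out rate of 20%, the sample size in this setting is determined to be 80 cases (40 per"). 30/(1 - 0.20) = 37.5, rounded up to 38, against 40 stated. The difference of 2 may be rounding or the unquantified allowance for miRNA validation. It has no bearing on this point.

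**Standard error of the contrast, in SD units.** sqrt(1/80 + 1/40) = 0.1936.

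**Case 1: matching succeeds.** The true standard error is 0.1936 x sqrt(1 - R2), but the unadjusted test uses 0.1936.
- True alpha = 2 x [1 - Phi(1.96/sqrt(1 - R2))].
- Power, unadjusted = Phi[(0.5/0.1936 - 1.96)/sqrt(1 - R2)].
- Power, adjusted = Phi[0.5/(0.1936 x sqrt(1 - R2)) - 1.96].

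| R2 | SE too large by | True alpha | Power unadjusted | Power adjusted | Points lost |
|---|---|---|---|---|---|
| 0 | 0% | 5.0% | 73.3% | 73.3% | 0 |
| 5% | 2.6% | 4.4% | 73.8% | 75.5% | 1.6 |
| 10% | 5.4% | 3.9% | 74.4% | 77.7% | 3.3 |
| 20% | 11.8% | 2.8% | 75.7% | 82.3% | 6.6 |

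A simulation of 40 sets of one control and two patients (4,000 runs) agrees in direction. With a within-set correlation of 0.1 the unadjusted t-test rejects in 4.2% of runs and the set-based analysis in 5.2%. With 0.3 the rates are 2.0% and 5.2%.

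**Case 2: matching leaves a gap.** Let rho = sqrt(R2) be the correlation of the factor with the marker.
- Shift of the test statistic: b = rho x gap/0.1936.
- False-positive rate = 1 - Phi(1.96 - b) + Phi(-1.96 - b).

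| rho (R2) | Gap | b | False-positive rate |
|---|---|---|---|
| 0.10 (1%) | 0.2 SD | 0.10 | 5.1% |
| 0.14 (2%) | 0.3 SD | 0.22 | 5.6% |
| 0.20 (4%) | 0.3 SD | 0.31 | 6.1% |
| 0.32 (10%) | 0.3 SD | 0.49 | 7.8% |
| 0.45 (20%) | 0.3 SD | 0.69 | 10.7% |
| 0.30 (9%) | 0.5 SD | 0.77 | 12.1% |

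This formula takes the gap as a systematic difference with full sampling variation around it. If instead the realised gap is exactly 0.3 SD, the spread shrinks by sqrt(1 - R2) and the two terms become 1 - Phi[(1.96 - b)/sqrt(1 - R2)] and Phi[(-1.96 - b)/sqrt(1 - R2)]. The rates at R2 of 10 and 20% are then 6.6% and 8.0%. The 8 to 11% is thus the upper end for a 0.3 SD gap.

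**The case against.** **This is an omission, not an error.** The miRNA section names no test for the contrast, and the statistical analysis plan, which is not shown, may supply an adjusted one. This stands in part. No claim can be made that the miRNA gate will be tested without adjustment. Still, the article does not leave group comparisons open: it names tests in three sections, and all are unadjusted.

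**The t-test and ANOVA sentence may not cover healthy volunteers.** It closes a section about patients in the verum and sham groups. This stands as an ambiguity. One-way ANOVA would suit three groups, but the text does not say so. The Kruskal-Wallis step concerns taxa, while the gate to week 4 is described only for miRNAs.

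**The effect is small.** This stands at low R2: at 5 to 10% about 2 to 3 points of power are lost, and with a weak correlation the false-positive rate barely moves.

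**Wrong admissions do limited harm.** This also stands in part. The week-4 comparison is between randomised arms, so a candidate admitted because of age or sex does not bias it. The harm is to the claim that the marker relates to constipation.

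**Stronger readings the protocol does not support.** A reader might infer that the standard errors are certainly wrong. They are right if age and sex do not predict the marker; if they do and matching succeeds, they are too large, which is conservative. A reader might also infer that 80 to 40 allows only group-level matching. Sets of one control and two patients are feasible; only 1:1 pairing of all patients is ruled out. Finally, a residual imbalance is possible, not shown.

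**Conclusion.** The point holds as an improvement at little cost. The protocol matches non-randomised controls on age and sex, names only unadjusted group tests, and names none for the miRNA contrast that forms the candidate pool.

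The size is modest and depends on assumed values of R2 and of the gap. Successful matching makes the unadjusted test mildly conservative and costs some power. A leftover gap raises false positives materially only when both the gap and the correlation are sizeable. All rates are per marker, by normal approximation. Adjusting for age and sex deals with both cases, so it is unnecessary to know in advance which will apply.

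**What to change.** State whether matching is individual (and in what ratio) or by frequency. For the baseline patient-healthy contrast on individual samples, that is taxa and miRNAs measured per person, use a linear model on suitably transformed or ranked values with group, age and sex as terms. If matching is individual, use the matched set in their place. Keep the unadjusted test as a check. Say which test applies to the miRNA contrast and whether the ANOVA and t-test sentence reaches the healthy group.

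The initial array on pooled samples has no individual values, so it cannot be adjusted in this way; the change applies from the individual-sample measurements onward.

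Cost: two degrees of freedom (with 120 subjects, 120 - 4 = 116 remain) and analysis wording. Age and sex are already known because they are the matching factors. No patients, samples or visits are added.

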#### Randomization

SCC participants will be divided into verum and sham acupuncture groups based on a randomization allocation card, which will be filled according to the random sequences generated by SPSS 25.0 software, including terms of random numbers, serial numbers, and allocation information, and enveloped and provided by visit order. The healthy subjects will be directly recruited as the healthy control without randomization.

#### Blinding

In this study, we will apply a type of sham acupuncture device to mask verum and sham acupuncture between patients from the two acupuncture treatment groups. The participants, other than the acupuncturists, will be single-blinded to receive treatment in separate consulting rooms, with the avoidance of communications. In the meantime, the outcomes assessors and statisticians who are responsible for statistical analysis will also be masked concerning group assignments in the process of performing this study and data analysis.

### Intervention

The Park Sham Placebo Acupuncture Device (PSD) will be used, plus a disposable sterile acupuncture needle (length 25–75 mm, diameter 0.30 mm) for the VA group and a disposable sterile retractable blunt needle with the same size for the sham acupuncture group.

All subjects will be assigned to receive acupuncture treatments for 16 times within 4 weeks, including 5 times a week on working days for the first 2 weeks, and 3 times a week (once every other day) on working day for the last 2 weeks. The operators should be acupuncturists with a certificate to practice and at least 5 years of professional qualification.

Other medications will not be allowed, except that bisacodyl (5–10 mg) and glycerin enema (110 ml) can be used for participants who fail to have a bowel movement for 3 or more consecutive days. If the patient does not respond to bisacodyl (5–10 mg) and glycerin enema, 1–2 tablets (5–10 mg) of enteric-coated bisacodyl will be permitted (11). Furthermore, the date, specific time, dose of bisacodyl or glycerin enema using will be recorded in the defecation diary and case report form (CRF).

#### Verum Acupuncture Group

The acupoints of bilateral ST25 (*Tianshu*), SP14 (*Fujie*), and ST37 (*Shangjuxu*) will be selected for acupuncture treatment, based on previous studies and high-quality randomized controlled trials (10–12), according to the National Standard Nomenclature and Location of Acupuncture Points 2006 (GB/T12346-2006) (Table 2 and Figure 2). Moreover, BL33 (*Zhongliao*), DU20 (*Baihui*), and DU24 (*Shenting*) will be used according to the individual situation; BL33 will be used for severe straining if any, DU20 and DU24 will be used for participants accompanied with the symptoms of anxiety and depression.

**Table 2 T2:** Acupoints and non-acupoints used in the acupuncture group.

**Acupoint**	**Location**	**Non-acupoint**	**Location**
ST25 (*Tianshu*)	On the middle portion of the abdomen, 2 cun lateral to the central of the navel (needled bilaterally)	Non-acupoint 1	On the middle of abdomen, 1 cun lateral to ST25 (*Tianshu*), the midpoint between ST25 and SP15 (*Daheng*) (needled bilaterally)
SP14 (*Fujie*)	On the lower abdomen, 1.3 cun below the central of the navel and 4 cun beside the anterior midline. (needled bilaterally)	Non-acupoint 2	On the lower abdomen, 1 cun lateral to SP14 (*Fujie*), between Stomach Meridian of Foot-Yangming and Spleen meridian of foot Taiyin (needled bilaterally)
ST37 (*Shangjuxu*)	On the outside of the lower leg, 6 cun below ST35 (*Dubi*), and on the connecting line between ST35 and ST41 (*Jiexi*). (needled bilaterally)	Non-acupoint 3	On the lateral side of the lower leg, 1 cun lateral to ST37 (*Shangjuxu*), between Stomach Meridian of Foot-Yangming and Gallbladder Meridian of Foot-Shaoyang (needled bilaterally)

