## Methods

### Objectives

This trial aims to (1) re-evaluate the pure therapeutic effect of acupuncture for SCC; (2) identify the correlation between the gut microbiota and fecal miRNAs in patients with SCC; and (3) investigate the interactions among acupuncture-induced improvement of constipation symptoms, changes of fecal miRNAs and regulation of intestinal microbiota.

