#### Inclusion Criteria

Participants meeting all the following conditions will be enrolled in this study:

Aged 18 to 60 years old;History of SCC for a minimum of 6 months before the screening visit, and the activity of symptoms last for at least 3 months;Two or fewer CSBMs per week, exertion in defecation, and lumpy or hard stools (Bristol Stool Form Scale [BSFS] ≤3) during the run-in period;No special eating habits and not accompanied by severe anxiety, depression, or other mental disorders (SAS or SDS score <75);No use of medicine for constipation during the 1 week before enrolment (except for rescue medicine), including intestinal microecological preparations, probiotics, etc.; no acupuncture treatment for constipation in the previous 1 month; no participation in any other ongoing trial;Volunteered to join this trial and signed the informed consent.

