#### Sham Acupuncture Group

The sham acupoints of ST25, SP14, and ST37 will be selected to perform sham acupuncture without skin penetration (Table 2 and Figure 2). We will formulate and follow the standardized step-by-step instructions and operations to use the same rituals in the VA and SA groups as far as possible. However, instead of penetrating the skin, the blunt needles will be retracted into the hollow needle handle without penetrating the skin or reaching *de qi*. The frequency and course of treatment will be the same as those in the VA group.

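### Symptom-triggered extra points (BL33, DU20, DU24) are given in the verum arm with no stated sham counterpart, so number of sites and tailoring are unmatched in triggered patients

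*Protocol article*

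**What the plan says.** All references are to the Protocol article.

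- **Verum Acupuncture Group.** Every verum patient is needled bilaterally at ST25, SP14 and ST37. Three further points depend on the patient's presentation: "BL33 will be used for severe straining if any, DU20 and DU24 will be used for participants accompanied with the symptoms" of anxiety and depression.
- **Sham Acupuncture Group.** The sites are listed as follows: "The sham acupoints of ST25, SP14, and ST37 will be selected to perform sham acupuncture without skin penetration". The section undertakes to write standard instructions "to use the same rituals in the VA and SA groups as far as possible", and it adds: "The frequency and course of treatment will be the same as those in the VA group". It mentions no add-on site and no symptom trigger.
- **Table 2.** It pairs ST25, SP14 and ST37 with Non-acupoints 1 to 3, all bilateral. BL33, DU20 and DU24 do not appear for either arm.
- **Objectives.** The first aim is to "re-evaluate the pure therapeutic effect of acupuncture for SCC".
- **Inclusion Criteria.** Entry requires "Two or fewer CSBMs per week, exertion in defecation, and lumpy or hard stools" during the run-in. On mental state, patients must be "not accompanied by severe anxiety, depression, or other mental disorders (SAS or SDS score <75"), so milder anxiety or depression is allowed.

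**The concern.** A sham comparison isolates needling only if the arms match on everything else the patient experiences. Here the verum arm can receive more sites, and a treatment visibly adapted to the patient's own complaint, while the sham arm as described gets a fixed set. Any specific effect of BL33, DU20 or DU24 belongs to the verum package and is not the complaint. What is unmatched is the non-specific part: extra sites, extra contact and individual tailoring.

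The outcomes are open to such effects. A complete spontaneous bowel movement, on which the primary outcome rests, requires the patient's sensation of complete evacuation. Stool form and PAC-QOL are self-reported. Severe straining triggers BL33, and change in straining is a secondary outcome, so the mismatch sits in the patients with most room to move on that scale. The week-4 miRNA comparison and the between-arm comparison of correlations use the same two arms and inherit the same mismatch.

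**Working it through.** The plan gives no figure on this point to reproduce. The check is a side-by-side reading and a count of sites.

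**Inputs from the article**

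- Core points: 3, each bilateral, in both arms (Verum Acupuncture Group, Table 2).
- Add-on points, verum only: BL33; DU20 with DU24 (Verum Acupuncture Group).
- Sessions: 16 in both arms (Intervention).
- Verum patients: 40 (Calculation of Sample Size).
- Verum manipulation: 10 s, three times, per acupoint (Verum Acupuncture Group).

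**Assumptions, not in the article**

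- BL33 is used on one or two sides.
- DU20 and DU24 are one site each.
- A trigger, once present, holds at all 16 sessions. The course totals are therefore a ceiling.

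**Site count**

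Sites per session = 3 × 2 + add-on sites. Course total = sites per session × 16. The core total is 6 × 16 = 96.

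| Patient | Verum sites per session | Sham sites per session | Verum course total | Excess over sham (96) |
|---|---|---|---|---|
| No trigger | 6 | 6 | 96 | 0 |
| Severe straining only | 7–8 | 6 | 112–128 | 16–32 |
| Anxiety/depression only | 8 | 6 | 128 | 32 |
| Both triggers | 9–10 | 6 | 144–160 | 48–64 |

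The excess is 1 to 4 sites per session and always falls on the verum side.

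**Can triggered patients enter?** Yes. Exertion at defecation is an entry requirement, so some patients can be expected to strain severely. Only severe anxiety or depression is barred.

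**What could this do to the responder difference?** Let q be the share of verum patients triggered, and d the rise in their response probability due to extra sites and tailoring alone. The verum-sham difference then shifts by q × d. The article gives neither value, so the following is illustration only:

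- q = 10%, d = 5 points: 0.10 × 5 = 0.5 points, or 0.005 × 40 = 0.2 verum patients.
- q = 25%, d = 10 points: 0.25 × 10 = 2.5 points, or 0.025 × 40 = 1 patient.
- q = 50%, d = 20 points: 0.50 × 20 = 10 points, or 0.10 × 40 = 4 patients.
- d = 0: no shift, whatever q is.

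**The case against.** The strongest reply is that this reads too much into a condensed article. Table 2 leaves out the add-on points for verum as well, so it is a table of core points and its silence on sham add-ons shows little. Figure 2, which locates acupoints and non-acupoints, is not available. The sham section does not say that its list is exhaustive, and its promise of standard instructions and matched rituals may cover mirrored add-ons. Patients are treated in separate rooms and kept from comparing notes, so a sham patient would not readily learn that others receive more sites. Severe strainers are randomised to both arms, so room to improve is balanced in expectation. The remaining mechanism, a non-specific effect of a few more sites, is unproven.

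Much of this stands. Table 2 alone proves nothing, the effect size is unknown, and overlap between the BL33 trigger and the straining outcome causes bias only if the extra sites or tailoring have an effect of their own. The reply does not supply a sham counterpart, however. The article is specific enough to state the add-ons and their triggers for verum, and equally specific about which sham sites are used. What it expressly equates between arms is frequency and course, not the number of sites or their selection. The ritual clause is qualified and names no add-on site or trigger. An acupuncturist following the text has nowhere to place a sham BL33, DU20 or DU24.

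**Conclusion.** The concern holds on the text as written. Patients without a trigger are matched at 6 sites in each arm. Triggered patients get 7 to 10 verum sites against 6 sham sites per session, with tailoring in one arm only. The counts rest on the stated assumptions about BL33 laterality and single sites for DU20 and DU24.

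The direction of any bias would plausibly favour verum, but this is not shown. Its size cannot be estimated, because neither the triggered share nor the non-specific effect is known. The illustrative 0.5 to 10 points reflects the assumed ranges and nothing more. The point does not invalidate the trial. It should be corrected because it weakens a sham comparison meant to isolate the effect of needling, and because the correction is easy. Confidence is medium, since the full protocol may already match the arms.

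**What to change.** 1. State in the Sham Acupuncture Group section that the same triggers apply in both arms.
2. Specify a matched non-penetrating sham site for each of BL33, DU20 and DU24, and add these to Table 2. The choice of sites is for the investigators.
3. Record each patient's indication for the add-ons before randomisation, so that knowledge of the arm cannot influence it. The schedule allows this: the treatment period is "preceded by a 1-week run-in phase after the screening visit", randomisation follows at week 0, and the anxiety and depression scores and run-in straining are already considered for eligibility.

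If the full protocol already mirrors the add-ons, one sentence saying so is enough.

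**Cost.** One sentence, up to three table rows and one baseline field. The verum points stay as they are, and no extra patients, visits or analyses are needed. Sham sessions lengthen slightly: if the verum manipulation schedule is mimicked, 3 × 10 s = 30 s per site, so 30 to 120 s for 1 to 4 sites, plus placement. The investigators must also check that the sham device can be used at the added sites.
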